#### Examination procedures

All patients meeting the inclusion/exclusion criteria will be eligible for participation. Patients who agree to participate will sign an informed consent document approved by the Institutional Review Board at the respective study site. A therapist blind to group assignment will perform all evaluation procedures. After obtaining informed consent, all subjects will then complete the remainder of the self-report questionnaires and a physical examination. The following self-report questionnaires will be completed by the patient at the baseline examination, demographic data, Numeric Pain Rating Scale (NPRS) [24], Pain Diagram [25], Oswestry Disability Questionnaire (OSW) [26], Fear-Avoidance Beliefs Questionnaire Work (FABQ) [19], Patient Global Rating of Change (GROC) [27]. Following completion of self-report measures the patient will undergo a standardized historical and physical examination. The questionnaires and the physical examination will be repeated following completion of the four-week treatment program. The OSW, NPRS, and GROC will also be completed after the first week (2 sessions) of treatment and at a 6-month follow-up.

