### Data analysis

We will recruit 60 patients per clinical site, for a total enrollment of 240 patients across the four geographical locations. A sample size of 240 patients will provide 93% power to detect a minimal difference of 5 points on the OSW assuming a common standard deviation of 10 points. A sample size of 60 within each geographical location will provide 83% power to detect a difference of 9 points on the OSW assuming a standard deviation of 10 points. This sample size will provide sufficient power to detect a minimum clinically important difference in the entire sample, and a moderate difference within a geographical location.

Descriptive statistics, including frequency counts for categorical variables and measures of central tendency and dispersion for continuous variables will be calculated to summarize the data. Baseline demographic data will be compared across treatment groups to assess the adequacy of the randomization. If appropriate, statistical adjustments will be made for baseline characteristics that are significantly different between groups. An intention-to-treat analysis will be utilized in which all participants will be analyzed in the group to which they were originally assigned. All drop-outs and the reason for dropping out of the study will be reported. An *a priori *alpha level of 0.05 will be used for all analyses. All data will be screened to ensure they meet the assumptions for the inferential statistical analyses described below. If they do not meet the necessary assumptions, appropriate non-parametric procedures will be utilized.

The primary aim will be tested with analysis of variance (ANOVA) using the change in OSW score from baseline to 4-weeks (OSW_Baseline _– OSW_4-weeks_) as the dependent variable. The independent variable will be treatment with three levels (lumbo-pelvic manipulation, alternative lumbar manipulation, lumbar mobilization). A second ANOVA will be conducted on the one-week OSW change scores to test for the presence of an immediate treatment effect. We will also repeat the ANOVA procedure for the 6-month follow up outcomes, and using pain rating as the dependent variable.

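### The intention-to-treat promise covers all participants, but the only stated primary analysis, a 4-week change-score ANOVA, by default uses only patients with a 4-week OSW and leaves out the 1-week score

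*Protocol article*

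**What the plan says.** All of the analysis statements are in the Data analysis section of the protocol article.

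- Population: "An intention-to-treat analysis will be utilized in which all participants will be analyzed in the group to which they were originally assigned".
- Primary test: "The primary aim will be tested with analysis of variance (ANOVA) using the change in OSW score from baseline to 4-weeks". Treatment, with three levels, is the only factor.
- Other time points: "A second ANOVA will be conducted on the one-week OSW change scores to test for the presence of an immediate treatment effect", and "We will also repeat the ANOVA procedure for the 6-month follow up outcomes".
- Losses: "All drop-outs and the reason for dropping out of the study will be reported".
- Size and power: "We will recruit 60 patients per clinical site, for a total enrollment of 240 patients across the four geographical locations", and "A sample size of 240 patients will provide 93% power to detect a minimal difference of 5 points on the OSW", with an SD of 10. The figure of 240 is enrolment, and no allowance for loss is made.

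On the data available, the Examination procedures section says: "The OSW, NPRS, and GROC will also be completed after the first week (2 sessions) of treatment and at a 6-month follow-up". With the baseline and end-of-treatment questionnaires, OSW is therefore scheduled at baseline, 1 week, 4 weeks and 6 months.

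**The concern.** The population sentence and the primary test do not meet. The dependent variable needs a 4-week OSW, and the article expects drop-outs but offers only to report them. The test as described can include every participant only if everyone attends at 4 weeks or if a step outside the article fills the gap.

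The design makes the unused 1-week score relevant. Under the Treatment section, the assigned technique is given only in the first two sessions, and all groups then have three weekly visits of the same exercise. The Background describes patients who fit the prediction rule as rapid responders, with success judged over two sessions. It is plausible, though the article does not say so, that some patients who have recovered or failed to respond by week 1 stop attending. The Blinding section says that patients cannot be blinded, so such loss could differ by technique. A 4-week comparison restricted to those who stayed would then be biased as well as smaller, and the score that best describes early response would play no part in correcting it. The three separate ANOVAs could also rest on three different sets of patients.

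**Working it through.** **Inputs from the Data analysis section:** N = 240; difference 5 points; SD 10; alpha 0.05; stated power 93%. Per site: N = 60; difference 9 points; SD 10; stated power 83%.

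**Assumptions, because the article does not give them:** equal allocation (80 per arm, 20 per arm per site); loss of 5% to 20%, equal in all arms; correlation of 0.5 to 0.8 between the 1-week and 4-week scores.

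**Step 1: reproduce the plan's power.** For a three-group one-way ANOVA with n per arm, the noncentrality is λ = n × Σ(mᵢ − m̄)² / SD², with 2 and 3n − 3 degrees of freedom.

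- Whole sample, means (0, 0, 5): m̄ = 1.667 and Σ = 2.78 + 2.78 + 11.11 = 16.67, so λ = 80 × 16.67 / 100 = 13.33. Power is 91.2%, against 93% stated.
- Per site, means (0, 0, 9): m̄ = 3 and Σ = 9 + 9 + 36 = 54, so λ = 20 × 54 / 100 = 10.8. Power is 82.5%, against 83% stated.

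A one-sided two-sample calculation comes closer to 93% (93.4% to 93.5%) but gives 87% to 89% per site and so misses 83%. The ANOVA with means (0, 0, δ) fits the two stated figures together best and is used below.

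**Step 2: complete-case power under loss**, same formula, means (0, 0, 5):

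| Loss at 4 weeks | n per arm | λ | Power |
|---|---|---|---|
| 0% | 80 | 13.33 | 91.2% |
| 5% | 76 | 12.67 | 89.6% |
| 10% | 72 | 12.00 | 87.8% |
| 15% | 68 | 11.33 | 85.8% |
| 20% | 64 | 10.67 | 83.5% |

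**Step 3: what the 1-week score can recover.** Suppose a fraction d lacks the 4-week score, everyone has the 1-week score, and the correlation is ρ. A likelihood-based model then gives approximately n_eff = 80(1 − d) / (1 − ρ²d).

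| d | ρ | n_eff per arm | Power | Gain over complete case |
|---|---|---|---|---|
| 10% | 0.5 | 72 / 0.975 = 73.8 | 88.7% | 0.9 points |
| 10% | 0.8 | 72 / 0.936 = 76.9 | 90.0% | 2.2 points |
| 20% | 0.5 | 64 / 0.950 = 67.4 | 85.5% | 2.0 points |
| 20% | 0.8 | 64 / 0.872 = 73.4 | 88.5% | 5.0 points |

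Any further precision from adjusting for baseline OSW and site is not counted here.

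**Step 4: bias.** If a fraction d of one arm is lost, the retained patients' mean change differs from the full arm's mean by d × (mean of lost − mean of retained). The treatment contrast shifts by the difference between arms in that product. The article gives neither term, so no figure follows from it.

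**The case against.** Four points can be made for the plan, and each has some force.

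First, a reader might infer that the plan excludes every patient without a 4-week OSW, and so breaks its intention-to-treat promise. Nothing in the article says so. Exclusion is what the ANOVA does by default, not a stated rule. Imputation may be set out in a full protocol or analysis plan that is not shown, and its absence from an article is no fault in itself. The population sentence is also chiefly about grouping by assignment, which the ANOVA respects. What stands is that the article fixes the model, the dependent variable and the single factor, and that this choice sits badly with a sentence covering all participants.

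Second, a reader might say that the 1-week and 6-month scores are ignored. They are not, since each has its own ANOVA. They are unused only in the 4-week comparison. Patients who leave before 4 weeks may have no 6-month score either, so the recoverable information is mainly at 1 week.

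Third, the longitudinal model also omits patients with no follow-up OSW at all. That is correct, and it is why the population sentence needs rewording whichever model is used.

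Fourth, the stakes can be overstated. Evenly spaced means (0, 2.5, 5) give 81.0%, 76.4% and 71.0% power at 0%, 10% and 20% loss. The low start comes from the least favourable pattern of means and has nothing to do with missing data. An illustration such as 15% loss in one arm with a 10-point gap (0.15 × 10 = 1.5 points) uses inputs with no source in the article, and carries over fully to the contrast only if the other arms have no similar loss. The Study sample section also excludes patients unable to keep the weekly schedule, which should limit loss.

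**Conclusion.** The point holds in a limited form. The article promises an analysis of all participants, yet its only stated primary analysis by default uses those with a 4-week OSW and takes nothing from the 1-week score in that comparison. Under assumed loss of 10% to 20%, with equal arms, SD 10 and means (0, 0, 5), complete-case power drops from 91.2% to between 87.8% and 83.5%, which is still above 80%. A longitudinal model would recover only about 1 to 5 points of that.

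The stronger reason to change is bias. If loss depends on early response and differs by technique, the complete-case contrast can be distorted, while a model that includes the 1-week score is protected to the extent that loss is missing at random given the observed scores. The direction and size of the bias cannot be stated, because the article gives no loss rate and no information on who leaves. It does not follow that the trial's result would be biased, or that the plan has abandoned intention-to-treat.

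**What to change.** Make the primary analysis one likelihood-based longitudinal model of OSW at 1 week, 4 weeks and 6 months, with treatment, time, treatment-by-time, baseline OSW and site, and an unstructured covariance across visits. Site belongs in the model because the Randomization section provides a separate list for each site. Name the 4-week treatment contrast as primary, and take the 1-week and 6-month contrasts from the same model. Keep the 4-week change-score ANOVA as a sensitivity analysis.

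State that the model includes all randomised patients with at least one follow-up OSW, in their assigned group, under missing-at-random, and word the intention-to-treat sentence to say the same. Report how many randomised patients in each arm have no follow-up OSW.

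The cost is slightly more analysis work. No extra visits, questionnaires or patients are needed.

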**Methods/Design:**

Consecutive patients with LBP referred to physical therapy clinics in one of four geographical locations who satisfy the CPR will be invited to participate in this randomized clinical trial. Subjects who agree to participate will undergo a standard evaluation and complete a number of patient self-report questionnaires including the Oswestry Disability Index (OSW), which will serve as the primary outcome measure. Following the baseline examination patients will be randomly assigned to receive the lumbopelvic manipulation used in the development of the CPR, an alternative lumbar manipulation technique, or non-thrust lumbar mobilization technique for the first 2 visits. Beginning on visit 3, all 3 groups will receive an identical standard exercise program for 3 visits (visits 3,4,5). Outcomes of interest will be captured by a therapist blind to group assignment at 1 week (3^rd ^visit), 4 weeks (6^th ^visit) and at a 6-month follow-up. The primary aim of the study will be tested with analysis of variance (ANOVA) using the change in OSW score from baseline to 4-weeks (OSW_Baseline _– OSW_4-weeks_) as the dependent variable. The independent variable will be treatment with three levels (lumbo-pelvic manipulation, alternative lumbar manipulation, lumbar mobilization).

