### Study sample

Two hundred forty subjects with LBP will be recruited from physical therapy clinics in four different geographical locations (60 subjects per location). These sites will provide a diversity of geographic and practice settings. A flow chart demonstrating patient recruitment, study design and timing of data collection can be seen in Figure 1.

The study will include patients who meet the following inclusion criteria:

**1**. Chief complaint of pain and/or numbness in the lumbar spine, buttock, and/or lower extremity

**2**. Oswestry disability score (OSW) of at least 25%

**3**. Age greater than 18 years and less than 60 years

**4**. At least four out of five of the following criteria:

**a**. Duration of current episode < 16 days (judged from the patient's self-report)

**b**. No symptoms extending distal to the knee (judged from the pain diagram)

**c**. Fear-Avoidance Beliefs Questionnaire work subscale (FABQ-W) score <19

**d**. At least one hip with >35° internal rotation range of motion (measured in prone)

**e**. Stiffness in the lumbar spine (judged from segmental mobility testing)

The following exclusion criteria will be used for this study:

**1**. Red flags noted in the participant's general medical screening questionnaire (i.e. tumor, metabolic diseases, RA, osteoporosis, prolonged history of steroid use, etc.)

**2**. Signs consistent with nerve root compression, this includes *any one*of the following:

**a**. Reproduction of low back or leg pain with straight leg raise at less than 45°

**b**. Muscle weakness involving a major muscle group of the lower extremity

**c**. Diminished lower extremity muscle stretch reflex (Quadriceps or Achilles tendon)

**d**. Diminished or absent sensation to pinprick in any lower extremity dermatome

**3**. Prior surgery to the lumbar spine or buttock

**4**. Current pregnancy

**5**. Past medical history of osteoporosis or spinal compression fracture

**6**. Inability to comply with treatment schedule (weekly sessions for four weeks)

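### The primary ANOVA on OSW change leaves out baseline OSW as a prespecified covariate: a valid analysis, but usually less precise than the collected data allow

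*Protocol article*

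**What the plan says.** The primary model is given in full in the protocol article, Data analysis: "The primary aim will be tested with analysis of variance (ANOVA) using the change in OSW score from baseline to 4-weeks". Its only explanatory term follows: "The independent variable will be treatment with three levels (lumbo-pelvic manipulation, alternative lumbar manipulation, lumbar mobilization". The abstract (Methods/Design) agrees: "The primary aim of the study will be tested with analysis of variance (ANOVA) using the change in OSW score". The same ANOVA is to be repeated at 1 week, at 6 months and for pain.

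The one route by which a covariate could enter is conditional: "If appropriate, statistical adjustments will be made for baseline characteristics that are significantly different between groups". The sentence before it reads "Baseline demographic data will be compared across treatment groups to assess the adequacy of the randomization". Neither sentence names OSW.

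Baseline OSW is available for every patient. It is collected at the baseline examination and is also an entry criterion: "Oswestry disability score (OSW) of at least 25" per cent.

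**The concern.** A change score fixes the slope of the 4-week score on the baseline score at 1. If the true slope is lower, patients who start higher tend to drop more, so part of the spread in change is explained by baseline and could be removed. An arm that happens to start higher will then look somewhat better in this particular trial.

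The article gives some reason to expect a slope below 1. Patients are selected for a minimum OSW, the scale stops at 0, and the Background defines response proportionally, as a reduction of at least 50%. If everyone's score halved, the slope would be 0.5. No section reports the slope, so this is an indication and not a measurement.

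The model is stated, so this is a fixed choice and not a detail left to an analysis plan. What is at stake is precision, and an imbalance rule that makes the primary model depend on a baseline significance test in a randomised trial.

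**Working it through.** **Inputs.** From Data analysis: 240 patients, 5 points, SD 10, stated power 93%; 60 per site, 9 points, SD 10, stated power 83%; alpha 0.05. Assumed: equal allocation (80 per arm, 20 per arm within a site), correlation r between baseline and 4-week OSW, baseline SD s0 and follow-up SD s1.

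**1. The plan's own figures.** For an overall F test the noncentrality is λ = n·Σ(μi − μ̄)²/σ².
- One arm 5 points from the other two: Σ = 16.67, λ = 80 × 16.67/100 = 13.33, power 91.2% (stated 93%).
- Same pattern within a site, 9 points: Σ = 54, λ = 20 × 54/100 = 10.8, power 82.5% (stated 83%).
- Evenly spaced means 0, 2.5, 5: Σ = 12.5, λ = 10, power 81.0%.

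A one-sided pairwise z test gives 93.5% for the whole trial but 88.5% within a site. Of the set-ups tried, only the one-arm-apart F test comes close to both stated figures.

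**2. Variance with and without the covariate (common slope b = r·s1/s0).**
- Change score: s0² + s1² − 2r·s0·s1.
- ANCOVA: s1²(1 − r²).
- Difference: (s0 − r·s1)² = (1 − b)²·s0², which is zero only when b = 1.

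Ratio of ANCOVA variance to change-score variance:

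| SD baseline, follow-up | r = 0.3 | r = 0.5 | r = 0.7 |
|---|---|---|---|
| equal | 0.65 | 0.75 | 0.85 |
| 10, 12 | 0.76 | 0.87 | 0.97 |
| 10, 15 | 0.87 | 0.96 | 1.00 |

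With equal SDs the ratio reduces to (1 + r)/2. As an example of the others, SDs 10 and 12 with r = 0.5 give 144 × 0.75/(100 + 144 − 120) = 108/124 = 0.87. With equal SDs, ANCOVA on about 156, 180 or 204 patients (240 × ratio) would match the change-score analysis of 240.

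**3. Power if SD 10 is the SD of change and the SDs are equal.** Residual SD = 10√ratio = 8.06, 8.66, 9.22 at r = 0.3, 0.5, 0.7, with one degree of freedom removed.
- One arm apart: 91.2% rises to 98.6%, 97.1%, 95.1%.
- Evenly spaced means: 81.0% rises to 94.7%, 91.2%, 87.2%.

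**4. Power if SD 10 is the SD of a single score.** The article says only "assuming a common standard deviation of 10 points". On this reading, with equal SDs, the SD of change is 10√(2(1 − r)) = 11.83, 10.00, 7.75. With one arm apart, power is 79.0%, 91.2%, 99.1% for change scores and 93.6%, 97.1%, 99.7% for ANCOVA.

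**5. Imbalance that the clause would miss.** With an assumed baseline SD of 10, the standard error of a pairwise baseline difference is 10√(2/80) = 1.58. Differences up to 1.96 × 1.58 = 3.1 points would not reach p < 0.05 in a pairwise test. With equal SDs the change score carries (1 − r) of that difference into the contrast: at most about 2.2, 1.5 or 0.9 points at r = 0.3, 0.5, 0.7, against a target of 5.

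**The case against.** The strongest reply is that nothing here is an error. In a randomised trial the change-score ANOVA is unbiased and keeps its type I error, and the planned power is already about 91% in the pattern that roughly reproduces the article's figures. All of that stands.

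A reader might go further than the article supports in four ways.
- **That the estimate is biased towards the arm with the higher baseline.** The shift is conditional on the imbalance that chance produces in one trial, and it averages to zero over randomisations.
- **That lost precision and chance imbalance are two separate harms.** They are one. The excess variance (1 − b)²·s0² is the imbalance carried into the estimate, and the ordinary standard error already includes it.
- **That ANCOVA can never be less precise.** With a common slope and large samples it is not. With arm-specific slopes it can be. Take slopes 1, 1 and 0, baseline SD 10, residual SD 6 and 80 per arm. For the contrast between the two slope-1 arms, the change score has variance 2 × 36/80 = 0.90. ANCOVA with the pooled slope of 2/3 has 0.90 + (1/3)² × 100 × 2/80 = 1.18. Simulation gave 0.91 and 1.19. The case is artificial, but it rules out an unconditional claim.
- **That the gain is worth a third more patients.** That needs equal SDs and r = 0.5 (1/0.75 = 1.33). With SDs 10 and 15 at the same r it is about 4% (1/0.964 = 1.04). Selection at a minimum OSW may compress the baseline spread and so shrink the gain, while a floor at 0 may act the other way.

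The conditional clause does not answer the point. It does not name OSW, and it acts only after a significant difference.

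**Conclusion.** The point holds as an efficiency recommendation, not as a flaw in validity. The stated primary model omits a baseline measurement held on every patient and is less precise than it need be unless the slope is 1.

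The size is uncertain because the article gives neither r nor the two SDs. Over the assumed values the variance saving runs from 35% to almost nothing. In the one-arm-apart pattern, with equal SDs and SD 10 as the SD of change, the gain is about 4 to 7 percentage points of power. With evenly spaced means it is about 6 to 14. Both ranges would shrink if the follow-up SD exceeds the baseline SD. All of these figures also assume a common slope and equal allocation.

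**What to change.** Analyse 4-week OSW (or OSW change, which gives the same treatment contrasts once baseline is in the model) by ANCOVA, with treatment as factor and baseline OSW as a prespecified covariate. Do the same at 1 week and 6 months, and use baseline NPRS for the pain analysis. Delete the adjustment triggered by significant baseline differences. While editing the paragraph, say whether the SD of 10 refers to change or to a single score.

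The cost is one sentence of analysis wording and one degree of freedom. No new data are needed, since OSW and NPRS are both already collected at baseline.

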## Discussion

We have presented the rationale for the need to determine the effectiveness of various thrust and non-thrust manual therapy techniques in patients with LBP who satisfy a CPR. The design we selected will allow for the analysis of the primary outcome measure (OSW) at 1 4 week, 4 weeks and at a 6-month follow-up. Results of this trial will be disseminated as soon as they become available.
